### Recruitment and retention

4.7

Participants are recruited from Djaalinj Waakinj and otolaryngology/audiology departments of approved Western Australian pediatric hospital sites (e.g. PCH). Families of children referred to Western Australian hospital sites are informed of the research through an opt-out letter, enabling them to learn of the research participation opportunity whilst preserving their autonomy [42]. Clinicians at Western Australian hospitals may also make direct referrals to the RCT using a consent-to-contact form, which permits research staff to contact families directly about research participation. The information sheet and consent form are sent electronically or by mail to families before their appointment, allowing all relevant family members (e.g. other parents, grandparents, Elders, etc.) to be fully informed about the study, even if they are unable to attend the appointment with the primary parent/carer to provide informed consent. Strategies to promote retention of families recruited from Western Australian pediatric hospital sites include provision of as required support to families via phone, text message, or by reviewing their child at unscheduled time points, flexibility in appointment scheduling to accommodate family needs, and the embedded MDT review process providing families a direct pathway to engage with the hospital system (see full explanation in ‘Clinical oversight’).

Eligible children and families from Djaalinj Waakinj who have provided consent to be contacted for future research are referred to the RCT by Djaalinj Waakinj study clinicians. Both Aboriginal and non-Aboriginal research staff are available to discuss the RCT with families and provide support throughout the informed consent process. Recruitment from the Djaalinj Waakinj pathway enables Aboriginal families to participate in research within a culturally safe, community trusted service [35,36]. The involvement of Aboriginal research staff in study recruitment and conduct, many of whom are well-connected within the local Western Australian south metropolitan community and have long-standing relationships with families participating in research, plays a vital role in upholding culturally safe, respectful research conduct with Aboriginal families [43,44]. Their involvement not only fosters trust and open communication but strengthens the connections between the research team and the community, enhancing participation and retention by ensuring RCT conduct is underpinned by local knowledge and values [43,44].

To acknowledge the time and contribution of families to the research and to support participant retention, enrolled families receive two vouchers intended to contribute towards grocery and fuel expenses. In addition, children will receive a goodie bag containing materials to support the completion of their allocated program (e.g. tissues [BBC only], soap, hand sanitizer, coloring in pages etc.). This approach to participant reimbursement was implemented as recommended by the Aboriginal Community Advisory Group (ACAG).

### Allocation-sequence generation, concealment, randomization, and blinding

4.8

Participants are randomly assigned to the intervention or control arm using a computer-generated list (R v4.1, block sizes 2, 4, 6, 8) [45], stratified by site (PCH, Djaalinj Waakinj, or other Western Australian hospital sites), OME class (unilateral or bilateral), and prior tympanostomy tube insertion (yes or no) (Fig. 3).

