### Sample size

4.6

Power analysis was used to understand the trial operating characteristics, assuming a range for the proportion of OME resolution in the control arm to be between 14 % and 20 % [16]. Assuming a moderate 13 % absolute increase in OME resolution at post-randomization in the intervention arm compared to the control arm and type one error controlled at 5 %, the power is estimated to be approximately 80 % for a maximum sample size of 250 participants. Accounting for 10 % loss-to-follow-up, the RCT intends to recruit up to 275 participants to achieve sufficient power to declare superiority of the BBC intervention plus hand hygiene.

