### Primary and secondary statistical methods

4.10

A Bayesian logistic regression model will be used for the primary analysis on the binary endpoint $Y_{i}\in \left\{0,1\right\}$ for participant i=1,2,…,N. Currently, there are two arms and three recruitment pathways, however the model is designed to allow additional arms or recruitment pathways to be introduced in the future. A participant may be randomized to arm j=0,1,…,J (where j=0 is the control arm and j=1 is the intervention arm) and be recruited via pathway r=0,1,…,R (where r=0 is the PCH otolaryngology/audiology outpatient departments, r=1 is the PCH otolaryngology surgical pathway, r=2 is Djaalinj Waakinj and r≥3 for other approved sites). Let $x_{i}$ and $\omega_{i}$ be vectors of length J and R and contain the arm allocation and recruitment pathway, respectively, for participant i. Here, $x_{ij}=1$ if participant i is allocated to arm j and $x_{ij}=0$ otherwise. Similarly, $\omega_{ir}=1$ if participant i is recruited via recruitment pathway r and $\omega_{ir}=0$ otherwise. We use a Bernoulli model with a logistic link function below:$$Y_{i}∼\text{Bernoulli}\left(\text{logi}t^{-1}\left(\pi_{i}\right)\right)$$$$\pi_{i}=\alpha +\sum_{j=1}^{J}x_{ij}\beta_{j}+\sum_{r=1}^{R}\omega_{ir}\gamma_{r}$$

Here, $\pi_{i}$ is the log odds of OME resolution between 4 and 6 weeks post-randomization for participant i. The log odds for a participant allocated to the control arm and recruited via the PCH otolaryngology/audiology outpatient pathway is α, and $\beta_{j}$ and $\gamma_{r}$ are the adjusted log odds ratios of arm j compared to the control arm and recruitment pathway r compared to the PCH otolaryngology/audiology outpatient pathway, respectively. We assign the following weakly informative prior probability distributions to the model parameters:$$\alpha ∼N\left(\text{logit}\left(0.17\right),0.3^{2}\right)$$$$\beta_{j},\gamma_{r}∼N\left(0,1\right)\;\forall j=1,\ldots ,J,r=1,\ldots ,R$$

The posterior distribution of the quantity of interest ($\beta_{1}$) will be estimated from the primary analysis and will be used to inform trial adaptation decisions.

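### Two of the three stratification factors, OME class and prior tubes, are absent from the primary model: a modest loss of efficiency whose repair must include the intercept prior

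*Protocol article*

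**What the plan says.** Section 4.8 describes an allocation list "stratified by site (PCH, Djaalinj Waakinj, or other Western Australian hospital sites"), together with "OME class (unilateral or bilateral), and prior tympanostomy tube insertion (yes or no").

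Section 4.10 opens with "A Bayesian logistic regression model will be used for the primary analysis on the binary endpoint" and then prints the linear predictor. Its two covariate vectors are said to "contain the arm allocation and recruitment pathway, respectively, for participant i". Pathway separates PCH outpatients, PCH surgical, Djaalinj Waakinj and other sites, so it covers the site stratum, and more finely than the randomisation does. OME class and prior tubes do not appear, and no reason is given. The only extension foreseen is for further arms or pathways.

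The priors are N(logit(0.17), 0.3²) for the intercept and N(0,1) for the arm and pathway coefficients. The posterior of β1 from this model feeds the section 4.11 rules: superiority if P(β1 > log 1.1) exceeds 0.975, futility if it falls below 0.05.

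**The concern.** Factors are usually chosen for stratification because they are thought to matter for the outcome, and the usual practice is to carry them into the analysis. In a logistic model, leaving out a prognostic covariate moves the treatment log odds ratio toward zero even when the arms are perfectly balanced. Here that makes the 0.975 threshold harder to reach at every look.

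OME class deserves particular attention. The endpoint is one binary value per child, and section 4.5 counts resolution only in ears that were type B at enrolment. Children therefore enter with either one or two ears at risk.

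**Working it through.** **1. Factors side by side.**

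| Factor | Stratified (4.8) | In primary model (4.10) |
|---|---|---|
| Site | yes | yes, through pathway |
| OME class | yes | no |
| Prior tubes | yes | no |

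**2. The plan's own power figure.** Section 4.6 gives about 80% with 250 participants (125 per arm), a control rate of 14% to 20%, a gain of 13 points and type I error of 5%. For two proportions, power = Φ[(Δ − z·SE0)/SE1]. At 17% v 30%, SE0 = √(2 × 0.235 × 0.765/125) = 0.0536 and SE1 = √((0.17 × 0.83 + 0.30 × 0.70)/125) = 0.0530. One-sided 5% gives (0.13 − 1.645 × 0.0536)/0.0530 = 0.79, or 78.5%. At control rates of 14%, 17% and 20% the results are 81.9%, 78.5% and 75.5% one-sided, and 72.4%, 68.1% and 64.5% two-sided. Simulating the printed model and rule, with looks at 100, 150, 200 and 250 and an assumed 40/20/40 pathway mix, gives about 63% to 72%. The comparisons below start from simulated power, not from 80%.

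**3. Is OME class linked to the endpoint?** An illustration, assuming 17% resolution per ear and independent ears:
- If one resolved ear suffices, a bilateral child resolves with probability 1 − 0.83² = 31%, against 17% for a unilateral child. The odds ratio is (0.311/0.689)/(0.17/0.83) = 2.2.
- If both ears must resolve, the probability is 0.17² = 2.9%. The odds ratio is about 0.15.

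Correlation between ears pulls both odds ratios toward 1. An association is plausible under either rule, but its direction depends on a rule that section 4.5 leaves open.

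**4. Power without and with the two terms.** Control 17%, intervention 30%, stratified sequential trials, both models fitted to the same data. Prevalences and odds ratios are assumptions.

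| Assumptions | Odds ratios (class / tubes) | Without | With | Gain |
|---|---|---|---|---|
| 50% bilateral, 30% tubes; intercept prior SD 1.5 in both models | 2 / 1.5 | 57.5% | 58.6% | 1.1 |
| same | 3 / 2 | 57.6% | 61.0% | 3.4 |
| same | 5 / 2 | 57.1% | 61.6% | 4.5 |
| 60% bilateral, 25% tubes; SD 0.3, prior re-centred in the adjusted model | 0.67 / 0.67 | 65.8% | 66.5% | 0.7 |
| same | 0.5 / 0.5 | 66.2% | 67.4% | 1.2 |
| same | 0.25 / 0.25 | 67.2% | 74.7% | 7.5 |

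If neither factor is prognostic, nothing changes beyond simulation error. In the re-centred scenarios the false-positive rate went from 1.3% to 1.3%, 1.4% to 1.3%, and 0.8% to 1.4%.

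**5. Where the gain comes from.** In the last row the average estimate of β1 moves from 0.685 to 0.768, while its posterior SD rises from 0.269 to 0.281. Distance from the threshold log 1.1 = 0.095, in SDs, goes from 0.590/0.269 = 2.19 to 0.673/0.281 = 2.40. The SD does not shrink; the effect moves further from zero.

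**6. Why the intercept prior must change too.** With centred covariates the intercept is the log odds at average covariate values. Under the assumed odds ratios this corresponds to 16.7%, 16.1% and 13.7%, not 17%. A prior with SD 0.3 held at 17% pulls the intercept up and β1 down.
- Centred terms under the printed prior: power falls from 67.7% to 66.6% (odds ratios 0.5) and from 68.0% to 64.3% (odds ratios 0.25).
- Reference-cell coding under the printed prior, odds ratios 0.25: the false-positive rate rises from 0.8% to 7.4%.
- Widening the prior to SD 2, neither factor prognostic, pathway-only model: power falls from 68.1% to 58.8%.

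**The case against.** The strongest case against is that no validity problem has been shown. Balance on the strata is secured by design, site is already in the model, and ignoring the other two factors leaves the false-positive rate equal or lower. That stands, and it limits this to an efficiency and consistency point.

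It is also fair that the documents give no resolution rate by OME class or prior tubes. A reader might infer that bilateral disease must raise the chance of resolution because there are two ears to clear. Section 4.5 does not say whether one ear suffices, so the direction is open, and for prior tubes the documents offer no argument either way.

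A reader might also infer that the omission overstates the posterior uncertainty of β1. It does not: the SD rises slightly on adjustment. The gain lies in power, or in precision on the risk-difference scale.

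Nor can the gap between about 63% to 72% and the stated 80% be put down to this omission. That gap appears even when neither factor is prognostic.

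The point cannot be set aside as detail for the analysis plan, because the article prints the full equation and priors and ties the stopping rules to them.

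**Conclusion.** The mismatch is explicit: two of three stratification factors are left out of the model behind the superiority and futility rules. If they are prognostic, the treatment log odds ratio is pulled toward zero and some power is lost. The loss is nil without prognostic value, about 1 to 4 points for moderate factors and about 5 to 8 for strong ones.

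These sizes rest on assumed odds ratios, prevalences and pathway mix. The re-centred results also set the prior mean from the assumed true odds ratios, which the sponsor will not know exactly, so they lean to the favourable side.

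A reader might infer bias or a raised risk of a false claim. The calculations show the opposite: the printed analysis is, if anything, conservative. The change is worth making, but not urgent on grounds of validity.

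**What to change.** - Add centred terms for bilateral OME and prior tubes to π_i, each with an N(0,1) prior, at every interim and at the final analysis.
- In the same step, re-centre or widen the intercept prior so that it is consistent with the centred covariates. Do not add the terms under the printed prior.
- Judge widening on its own merits, because it lowers power relative to the present tight prior. With SD 2 and both terms added, power was 60.0% (odds ratios 0.5) and 61.8% (odds ratios 0.25), against 67.7% and 68.0% for the printed model.
- Rerun the operating-characteristic simulations before the next interim, over a range of prognostic strengths in both directions, to confirm that the thresholds still control type I error and power.
- Keep the pathway-only model as a sensitivity analysis.

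The cost is a revised prior and a simulation rerun. Both variables define the strata and are known before randomisation, so no new data collection is needed.

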**Fig. 3 fig3:**
[figure not shown]
Study flow.

The RCT follows a blinded outcome assessment design; screening, enrolment, and randomization are conducted by unblinded researchers with knowledge of arm allocations, whilst all visits from post-randomization to study completion are managed by researchers blinded to arm allocations (Fig. 3). An unblinded statistician created and uploaded the randomization sequence into REDCap, the secure electronic research database. To safeguard blinding, staff receive training in blinding procedures, and access to sensitive data (e.g. randomization sequence files, REDCap randomization module) is restricted to designated unblinded staff only. Study materials are prepared in opaque envelopes, identifiable only to unblinded staff to mitigate unintentional unblinding. Should unintentional unblinding occur, future participant follow-up is reallocated to a different blinded researcher. Emergency unblinding is generally unnecessary, as blinded researchers can refer participant safety or other concerns directly to unblinded colleagues in real-time. The study has recruited sufficient personnel to ensure both blinded and unblinded researcher roles are adequately staffed at all times. Additionally, contingency plans are in place to preserve blinding integrity in the event of any staffing challenges.

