**Methods:**

This parallel-group, 1:1, outcome assessor-blinded, individual adaptive RCT investigates whether completing the BBC intervention plus hand hygiene twice-daily at home increases OME resolution after 4-to-6 weeks in children with OME, compared to hand hygiene alone. Families (n = 250) perform their individually randomized program (BBC plus hand hygiene, or hand hygiene only) at home. The primary outcome is the difference in OME resolution rates between trial arms, assessed using tympanometry (type B to A or C_1_ transition) and otoscopy. Secondary outcomes include natural OME resolution, discharges from tertiary care, family satisfaction, hearing thresholds, QoL, bacterial load in the nasopharynx and on hands, cost comparison within the RCT versus standard care, and adverse events. All outcomes are measured by blinded researchers. An intention-to-treat analysis will be performed on all randomized participants. Guided by an Aboriginal Community Advisory Group, the RCT ensures culturally appropriate research whilst addressing community priorities in managing childhood ear disease.

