### Interventions and comparators

4.4

This study has two arms: the BBC program intervention plus hand hygiene, and a hand hygiene only program control. Families in the intervention arm receive the BBC intervention routine (Fig. 1) to perform at least twice daily for four-to-six weeks, which incorporates the hand hygiene program steps (Fig. 2) [28,37]. The control arm families receive a hand hygiene program in line with Centers for Disease Control and Prevention guidelines, for completion at least twice-daily for four-to-six weeks (Fig. 2) [37]. Trained research staff deliver both programs by conducting interactive demonstrations using step-by-step guides and checklists, and by providing educational materials containing visual prompts to guide program completion. Both arms receive watchful waiting, supportive care, and ear health education (Table 1) [17,38]. Use of ear-specific treatments (e.g. ear candles, EarPopper®, nasal sprays etc.) are prohibited during the four-to-six-week intervention/control period to avoid contamination of the assigned program, with any use of these monitored at each study visit by collecting updated medical histories (Table 2). Adherence is tracked through weekly text message surveys regarding program completion frequency (Table 2). Hand hygiene is recommended by the National Health and Medical Research Council (NHMRC) *Staying Healthy* guidelines to reduce the spread of communicable disease in children, and is embedded within the BBC intervention [39]. It was selected as the control to isolate the effects of blowing the nose, breathing, and coughing on the presence of middle ear fluid whilst engaging control group families in a beneficial, evidence-based hygiene practice [4,29].

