**Fig. 2 fig2:**
[figure not shown]
Steps for the hand hygiene program [37].

**Table 1 tbl1:** Explanation of additional care provisions within study arms.

**Watchful waiting**	Conducting ear and hearing health assessments at scheduled and as needed time points, with care escalated as clinically indicated.
**Supportive care**	Encouraging parent/carer(s) to raise any questions or concerns about their child's ear health with the research team during study appointments or via phone/text message and to arrange an unscheduled visit as needed or clinically appropriate.
**Generic ear health education resources**	Provision of an information sheet published by the Child and Adolescent Health Service about glue ear (OME).

**Table 2 tbl2:** Data collection timepoints.

Timepoints	Week 0	Weeks 4–6	Weeks 24–32	Any timepoint
	ScreeningEnrolment	Post-randomization	Final follow-up	Unscheduled visit
Informed consent	•			
Eligibility	•			
Randomization	•			
Medical history	•	•	•	•
Family history	•	**×**	**×**	**×**
Sociodemographic data	•	**×**	**×**	**×**
Otoscopy	•	•	•	•
Tympanometry	•	•	•	•
Audiometry	•	•	•	•
OAE	•	•	•	•
OM-6	•	•	•	•
PLUM	•	•	•	•
HATS	•	•	•	•
Adherence survey (via SMS)	Administered weekly between timepoints			
Intervention program performance checklist	•	•	**×**	**×**
Intervention program parent/carer understanding checklist	•	**×**	**×**	**×**
Motivational outcomes		•	•	**×**
Nasopharyngeal and palm specimen	•	•	**×**	**×**
Adverse event monitoring	Continuous			

• - mandatory; **× -** optional.

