### Outcomes

4.5

The primary outcome measure is the proportion of children that experience OME resolution in the intervention arm compared to the control arm, assessed through tympanometry. Tympanometry is a diagnostic test of middle ear function using parameters such as peak pressure, compliance, and ear canal volume, which tracks the transition from type B result (indicative of OME) at enrolment (week 0) to a type A result (normal) or type C_1_ result (Eustachian tube dysfunction, suggesting resolving OME) at post-randomization (week 4-to-6) (Table 2) [30,40]. For this study, a type A tympanogram is defined as a peak pressure of > −100 daPa, a type B tympanogram has an indeterminable peak pressure, a type C_1_ tympanogram as a peak pressure of between −100 and −199 daPa, and a type C_2_ tympanogram as a peak pressure of −200 to −400 daPa [41]. Type C_1_ tympanograms will be considered indicative of resolved OME in addition to type A tympanograms, as the literature suggests type C_1_ may reflect a transient or resolving stage of middle ear effusion, rather than a persistent form of OME requiring intervention [16,41]. Resolution can be unilateral or bilateral, however the primary outcome will only be considered in any ears that produced type B tympanograms at enrolment. Type C_2_ tympanogram findings will be considered indicative of ongoing middle ear dysfunction. The efficacy of the BBC intervention will be considered clinically meaningful if it results in a number needed to treat to benefit (NNTB) of 10 or less for the resolution of OME.

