### Data collection and management

4.9

This RCT uses multiple diagnostic tools to assess ear health and function for outcome evaluation. The hearScope™ video-otoscopy device visualizes the external auditory canal and tympanic membrane, whilst tympanometry using the Interacoustics Titan Middle Ear Analyzer detects middle ear fluid causing conductive hearing loss [46,47]. Hearing sensitivity levels (pure-tone audiometry) are tested using the hearScreen® Smartphone Screening Audiometer [48], and the Interacoustics Titan Middle Ear Analyzer assesses inner ear health (cochlea outer hair cell function) via otoacoustic emissions to identify sensorineural hearing loss [49].

The OM-6 questionnaire evaluates health-related QoL in children with recurrent OM [50], and the PLUM and HATS are culturally appropriate questionnaires which aid in early detection of hearing and speech issues by gauging parent/carer perceptions of their child's hearing and speech [51,52]. A motivational outcomes questionnaire, developed using components of the Self Determination Theory Treatment Self-Regulation Questionnaire and the Perceived Competence Scale, measures the autonomous motivation of families to complete their assigned program, their perceived confidence and self-efficacy relating to program participation, and the extent to which its outcomes have met their expectations using a seven-point Likert scale [53].

In line with the RE-AIM framework, used in public health and implementation science to assess the impact and sustainability of health interventions, data to assess the implementation fidelity of the BBC intervention plus hand hygiene within the RCT will be collected using structured checklists [54]. These checklists include the assessment of the quality of intervention delivery at enrolment and quality of intervention performance at enrolment and post-randomization, along with a parent/carer checklist to confirm their level of understanding of the intervention at enrolment (Table 2) [54].

All research staff receive specialist training in study procedures (clinical and non-clinical) to ensure accuracy and reliability, along with International Council for Harmonization Good Clinical Practice (ICH-GCP) training to uphold standards in ethical conduct, data handling, and participant safety [55].

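### The programme performance checklist is mandatory at the primary-outcome visit, which the plan says blinded researchers manage; scoring it discloses the arm, and nothing keeps it away from the assessor

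*Protocol article*

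**What the plan says.** All references are to the protocol article.

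- **Who runs follow-up.** Section 4.8 gives screening, enrolment and randomization to unblinded staff. After that, "all visits from post-randomization to study completion are managed by researchers blinded to arm allocations". The abstract adds: "All outcomes are measured by blinded researchers".
- **When the primary outcome is read.** Section 4.5 defines resolution by a change in tympanogram type from enrolment to the post-randomization visit at weeks 4–6.
- **What else happens at that visit.** Table 2 has a row headed "Intervention program performance checklist", with a bullet at week 0 and at weeks 4–6. The legend defines a bullet as mandatory. Section 4.9 confirms the timing in prose: the checklists cover "quality of intervention performance at enrolment and post-randomization".
- **What the checklist is for.** Section 4.9 says that "data to assess the implementation fidelity of the BBC intervention plus hand hygiene within the RCT will be collected using structured checklists".
- **What separates the arms.** Both arms do hand hygiene. On the choice of control, section 4.4 says: "It was selected as the control to isolate the effects of blowing the nose, breathing, and coughing on the presence of middle ear fluid".
- **What happens after unblinding.** Section 4.8: "Should unintentional unblinding occur, future participant follow-up is reallocated to a different blinded researcher".

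**The concern.** Families know which programme they were taught, so the trial relies on the blinded assessor for its protection against biased measurement. The abstract and the design statement both claim that protection.

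The visit schedule places a task that reveals the arm at the visit where the primary outcome is measured, and the blinding section says blinded researchers manage that visit. If staff follow both statements as they stand, the person taking the tympanogram may know the allocation before or while taking it. The other measurements at that visit (otoscopy, audiometry, otoacoustic emissions and the parent questionnaires) would be exposed in the same way. A reading taken with knowledge of the arm cannot be made blind afterwards.

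**Working it through.** The article gives no figure to reproduce on this point and no arithmetic applies. The check is a cross-reading of its statements.

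1. **Same visit?** Yes. Section 4.5 times the primary tympanogram at weeks 4–6. Table 2 makes both tympanometry and the performance checklist mandatory at weeks 4–6. Section 4.9 repeats the checklist timing in words, so the table entry is not an artefact of a broken table.

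2. **Does the checklist reveal the arm?** There are two ways to read it.
   - If it is completed in both arms, the scorer rates either the blow, breathe and cough routine plus hand hygiene, or hand hygiene alone. By the design in section 4.4, that difference is the allocation.
   - If it is completed only for intervention families, as the fidelity wording in section 4.9 would allow, its use or absence is the allocation.

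   Under both readings the scorer learns the arm. This is an inference, but a near-certain one. It does not depend on whether the child or the family performs the routine.

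3. **Is the task kept away from the assessor?** Nothing in the text does so. Section 4.8 gives visits from post-randomization onward to blinded researchers without exception. No section assigns the weeks 4–6 checklist to an unblinded colleague, and none places it after the outcome measurements.

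4. **Do the other safeguards reach it?** Section 4.8 lists staff training, restricted access to randomization data and opaque envelopes. The access limits and envelopes protect files and materials. They do not stop a person who scores a performance from seeing what is performed.

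5. **Does the remedy reach it?** No. Reallocation applies to future follow-up after unintentional unblinding. It cannot protect a tympanogram taken at the visit where the disclosure occurs, and a scheduled mandatory task is hard to call unintentional.

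6. **How much room is there for bias in the primary outcome?** Section 4.5 classifies by peak pressure: type A above −100 daPa, C1 from −100 to −199 daPa, C2 from −200 to −400 daPa, and type B when no peak can be determined. A and C1 count as resolved; C2 does not. Discretion remains in accepting the probe fit, in repeating a trace, in judging whether a peak is determinable, and near the C1/C2 boundary at −199/−200 daPa. The abstract also names otoscopy in the primary assessment, which leaves more to judgement. The documents give no rate at which such choices change a classification, so the bias cannot be sized from them.

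**The case against.** The strongest reply is that loss of blinding is inferred. Managing a visit need not mean carrying out every procedure in it. The abstract's sentence concerns outcomes, and the fidelity checklist is not among the outcomes listed in section 4.5. An unblinded colleague could complete it, since section 4.8 says both roles are staffed at all times. Who fills in a form, and in what order, is detail that an article often leaves to the full protocol. Section 4.8 also refers to Fig. 3, which is not shown here.

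Part of this stands. The article does not say that a blinded researcher completes the checklist, so it would be wrong to say that blinding has been shown to fail. But the statement about visits carries no exception and the schedule mandates an arm-revealing task at one of them. Those are two stated rules that need reconciling, rather than a detail left out.

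It also stands that tympanometry is instrument-based with numeric cut-offs, and that section 4.9 describes electronic storage of the de-identified data. Both limit the bias; neither removes it.

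Three stronger readings are tempting and are not supported:

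- **A numerical inflation of the treatment effect.** A reader might assume some share of unresolved readings tips to resolved and compare the result with the 13-point target in section 4.6. Any such share would be invented.
- **Failure at weeks 24–32 as well.** A reader might infer that the same researcher stays unblinded. The reallocation rule, where applied, passes that visit to a different blinded researcher.
- **Disclosure through the motivational questionnaire.** It is mandatory at weeks 4–6, but section 4.9 describes Likert items on motivation, confidence and expectations. Nothing shows that these reveal the arm.

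The possibility that a child performs the routine just before tympanometry rests only on silence about order. The point does not need it.

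**Conclusion.** The concern holds as a conflict between stated rules. Read literally, sections 4.8 and 4.9 and Table 2 do not secure the assessor blinding claimed for the primary outcome, and the stated remedy cannot restore it at that visit. Every child who attends at weeks 4–6 is affected.

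The size and direction of any bias are unknown. The conclusion rests on two assumptions: that scoring the checklist discloses the arm, which follows almost directly from how the programmes differ, and that no unseen document or figure already separates the checklist from the assessor. If one does, the article only needs to say so.

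**What to change.** State in section 4.8 and in a note to Table 2 that at weeks 4–6:

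1. the blinded researcher completes and records all outcome measurements first;
2. an unblinded researcher then completes the performance checklist, out of the assessor's sight;
3. this is an exception to the rule that blinded researchers manage all visits from post-randomization onward.

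It would help to lock the outcome entries before step 2 and to log any unblinding at this visit. Moving the motivational questionnaire to step 2 is optional.

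The cost is wording and minor visit scheduling. Section 4.8 already says that both staff roles are covered at all times. The sample size, the endpoint and the primary model are unchanged.
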